### Sample size

The primary outcome of this study is children’s anxiety at anaesthesia induction as measured by the mYPAS-SF. Our estimate of effect is based on the validation study of ‘Take5’ in a cohort of children with burn-injuries (unpublished) and the ADVANCE preparation program [14]. Assuming a clinically meaningful difference in anxiety (15-point difference on the mYPAS-SF) [8, 14], with a mean control group score = 55 and a mean intervention group score = 40, a corresponding effect size of 0.61 was used for these analyses. Therefore, a sample of 50 participants per group is anticipated to provide > 90% power to detect this effect size (α < 0.05).

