### Hypotheses

Based on its prior initial success, it is expected that a ‘Take5’ video tailored to the peri-operative context will demonstrate significant reductions in peri-operative child anxiety and improve post-operative outcomes. Specifically, it is hypothesised:Children in the Take5 intervention group will demonstrate less peri-operative distress behaviours than children in the control group.Children in the Take5 intervention group will report less peri-operative anxiety than children in the control group.Parents in the Take5 intervention group will report less peri-operative anxiety than parents in the control group.

Secondary hypotheses are:Children of parents in the intervention condition will experience lower rates of post-operative pain scores and emergence delirium scores, and faster time to discharge compared to children in the control group.Children in the Take5 intervention will have improved health-related quality of life scores and reduced behavioural difficulties including symptoms of anxiety and depression at 3 months after the surgery compared to children in the control group.Parents in the Take5 intervention will report less general anxiety and depressive symptoms at 3 months after their child’s surgery compared to parents in the control group.

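### The stated power of more than 90% holds only for a one-sided 5% test that the protocol never declares; with a two-sided 5% test it is about 85.5%

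*Protocol article*

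**What the plan says.** The Sample size section of the protocol article sizes the trial on a single continuous outcome: "The primary outcome of this study is children’s anxiety at anaesthesia induction as measured by the mYPAS-SF". The target is a 15-point difference, "with a mean control group score = 55 and a mean intervention group score = 40", and "a corresponding effect size of 0.61 was used for these analyses". No standard deviation is printed. The conclusion is that "a sample of 50 participants per group is anticipated to provide" "> 90% power to detect this effect size". The significance level appears only at the end of that sentence: "to detect this effect size (α < 0.05").

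Three other sections bear on the point:

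- **Sequence generation** describes 100 envelopes split equally between the arms, so allocation is 1:1.
- **Hypotheses** is worded directionally, for example "Children in the Take5 intervention group will report less peri-operative anxiety than children in the control group".
- **Statistical methods** plans general linear models with control variables. It gives neither the number of sides nor any assumed covariate correlation.

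**The concern.** The Sample size section prints every input to the power calculation except the number of sides of the test. At 50 per group and an effect size of 0.61, that missing item moves the result from one side of 90% to the other, so a reader cannot tell whether the claim is true as written. Someone who assumes the usual two-sided 5% test will not be able to reproduce it.

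The figure is the trial's statement of how likely it is to detect its own target effect on the sizing outcome. If the test is two-sided, a non-significant result is more compatible with a true 15-point benefit than the protocol suggests. If the test is one-sided at 5%, the false-positive rate in favour of Take5 is 5%, against 2.5% in that direction for a two-sided 5% test. Readers would need to be told that.

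**Working it through.** **Inputs**

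- Difference: 55 − 40 = 15 points (Sample size).
- Effect size: d = 0.61 (Sample size). Implied SD = 15 / 0.61 = 24.6; this is derived, not stated.
- n = 50 per group, 1:1 (Sample size; Sequence generation).
- Alpha = 0.05, sides not stated (Sample size).

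**Set-up.** For two independent means, the noncentrality is d × √(n/2) = 0.61 × √25 = 3.05, with 2 × 50 − 2 = 98 degrees of freedom.

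**Step 1: reproduce the stated figure.** Normal approximation: power = Φ(3.05 − z), where z is the critical value. Exact: the probability that a noncentral t (98 df, noncentrality 3.05) exceeds the t critical value.

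| Test | z | Normal approximation | Noncentral t |
|---|---|---|---|
| One-sided 5% | 1.645 | Φ(1.405) = 92.0% | 91.7% |
| Two-sided 5% | 1.960 | Φ(1.090) = 86.2% | 85.5% |

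The claim of more than 90% is met one-sided and not met two-sided.

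**Step 2: is rounding the cause?** An effect size printed as 0.61 could lie between 0.605 and 0.615. Two-sided power over that range is 85.0% to 86.1%. Rounding does not close the gap.

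**Step 3: what would give 90% two-sided?**

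- Sample size at d = 0.61: n = 2 × (1.960 + 1.282)² / 0.61² = 56.5, so 57 per group by the normal approximation. The noncentral t gives 57.5, so 58 per group.
- Effect size at 50 per group: (1.960 + 1.282) × √(2/50) = 0.648 by the normal approximation, and 0.655 by the noncentral t. At the implied SD, 0.655 × 24.6 = 16.1 points.

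One-sided, 47 per group would be enough for 90%. Fifty per group is thus consistent with a one-sided calculation, but that does not show one was used.

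**Step 4: risk of missing the target effect.** Two-sided, 100% − 85.5% = 14.5%. The stated power implies under 10%.

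**The case against.** The strongest reply is that the protocol nowhere says two-sided. The hypotheses are directional, the abstract calls the trial a superiority trial, and the printed inputs give 91.7% with a one-sided 5% test. On that reading the figure is correct. This stands as far as it goes. A reader might infer flatly that the design fails to deliver its stated power, and the document does not support that, because it leaves the sidedness open. Nor does it support the opposite inference, that a one-sided test was knowingly used: a directional hypothesis states what is expected, not which test will be applied.

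A second reply is that sidedness may be fixed in the analysis plan or full protocol, neither of which is shown. That is fair for sidedness alone. The power figure, however, is stated in this article and can be checked only if the reader knows the number of sides.

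A third reply is that 85.5% belongs to an unadjusted comparison, whereas the planned analysis is a general linear model with control variables. Adjustment could raise power: two-sided 90% would be reached at a covariate–outcome correlation between about 0.35 (89.7%) and 0.40 (90.9%). The limitation on the 85.5% is accepted. It does not rescue the stated figure, because the power statement assumes no such correlation. Table 1 also schedules no anxiety measure before allocation, so the most obvious covariate is not available as a true baseline.

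**Conclusion.** The point holds in conditional form. The statement of more than 90% power is true for a one-sided 5% test (91.7%), which the protocol does not declare. It is not true for the conventional two-sided 5% test, where an unadjusted comparison has about 85.5%, a shortfall of at least 4.5 percentage points. This rests on the protocol's own effect size and group size, a two-sample comparison of means, and all 50 per group contributing data.

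A reader might go further and call the trial underpowered. That does not follow: two-sided power still exceeds 80%, and neither the design nor the treatment estimate is affected. The statement should be corrected, but it does not threaten the trial.

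**What to change.** State the sidedness in the Sample size section, write alpha as a fixed level instead of an inequality, and make the power agree. If the test is two-sided, suitable wording would be: *With 50 per group, an effect size of 0.61 (15 points, implied SD 24.6) and two-sided α = 0.05, power is about 85%.*

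If a one-sided 5% test was intended, say so, justify it, and carry the same test into the Statistical methods section so that sizing and analysis match. The figure of more than 90% can then stay.

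The two-sided correction costs one sentence and a slightly less favourable figure; the one-sided route also needs a line in the analysis section. Neither needs extra patients or a new assessment.

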### Recruitment

The clinical research assistant (social worker with psychology training) will perform recruitment, obtain written informed consent, provide the Take5 video intervention as per randomisation through sealed envelopes, video record the anaesthetic induction and undertake data collection. All participant data will be scored under interrater reliability by another member of the research team blinded to group allocation.

Patients who are scheduled for elective surgery will be screened for eligibility by a trained research assistant daily (weekdays) by reviewing the elective surgery list. Eligibility for the study will be confirmed with the rostered consultant anaesthetist. Participants who meet eligibility criteria will be approached to participate by the research assistant while at the Holding Bay on the day of surgery prior to receiving the anaesthetic induction. If the research assistant considers the parent to be under significant psychological distress some normalisation of the experience and follow up care will be provided to the participant as part of duty of care. A record of all patients screened exclusion criteria and reason for refusal will be recorded by the research assistant.

Recruited parents will be asked to report the levels of anxiety for themselves (parent) and their child. Parents allocated to the control group will be asked prior to the anaesthetic induction, whereas parents in the intervention group be asked after receiving the video intervention. Both groups will be filmed during their anaesthetic induction and parents will be asked to report their own and their child's anxiety levels during and after induction, and their own satisfaction level with the anaesthetic induction experience. Care will be taken to ensure the filming is unobtrusive and will not increase the child’s or parent’s anxiety. All participants will receive questionnaires after 3 months post-surgery to follow up on their mental and physical outcomes.

## Methods: assignment of interventions

### Allocation

#### Sequence generation

Numbers 1 to 100, equally identifying “intervention” and “control”, were manually allocated to individual envelopes. Once envelops were sealed, sequencing occurred through randomisation by a third party who unsystematically rearranged the sealed envelopes. The RA is blinded to the final sequence making the selection between intervention and control unpredictable.

#### Concealment mechanism

The envelopes will be prepared by a third-party separate to the trial; however, masking the research assistant, patient and their parent to the treatment allocation will not be possible.

#### Implementation

After consent is obtained, the research assistant will open a sealed envelope to determine whether participants are in the intervention and control group.

#### Blinding

Clinical staff (anaesthetic doctors and nurses) will be blinded to the treatment allocation. As induction will be filmed, the researcher responsible for coding the behavioural measures will also be blinded to treatment allocation.

## Methods: data collection, management, and analysis

### Data collection and methods

The research assistant will collect data on primary/secondary outcomes by observation, chart audit, and from staff and patient families during the peri-operative phases. To ensure inter-rater reliability and to prevent having too many people in the room when the child is having their anaesthetic, induction will be filmed allowing a second blinded investigator to score the child’s anxiety. Follow-up data will be collected using a purpose-built, online survey. A timeline of study participation and measures is summarised in Table 1.

**Table 1 Tab1:** Standard Protocol Items: Recommendations for Intervention Trials (SPIRIT 2013) schedule of study recruitment, intervention, and assessments

	*Study period*					
	*Enrolment*	Allocation	*Post-allocation*			
Timepoint	* − t*_*1*_	0	*t*_*1*_	*t*_*2*_	*t*_*3*_	*t*_*4*_
Enrolment:						
Eligibility screen	X					
Informed consent	X					
Allocation		X				
Interventions:						
Take5			X			
Control (Standard Care)			X			
Assessments:						
Visual Analogue Scale—Anxiety (VAS-A)			X	X		
Modified Yale Preoperative Anxiety Scale Short Form (mYPAS-SF)			X	X		
Perioperative Adult–Child Behavior Interaction Scale (PACBIS)			X	X		
Induction Compliance Checklist (ICC)			X	X		
Cornell Assessment for Pediatric Delirium (CAP-D)					X	
Face, Legs, Activity, Cry, Consolability Scale (FLACC)					X	
Parent rated acceptability of Take5 Video (*n* = 10)				X		
Parent rated satisfaction of clinical service						X
Patient-Reported Outcome Measures Early Childhood (PROMIS EC) – Child 3–5 years						X
Patient-Reported Outcome Measures (PROMIS) – Child 6–10 years						X
Child Health Utility 9D (CHU9D)						X
Depression Anxiety and Stress Scale (DASS-21)						X

### Reliability of measures

Modified Yale Preoperative Anxiety Scale Short Form (mYPAS-SF) (α = 0.92) [35]Peri-operative Adult–Child Behavior Interaction Scale (PACBIS) (Kappa range 0.62 to 0.94) [36]Induction Compliance Checklist (ICC) (α = 0.99) [38]Depression, Anxiety and Stress Scale 21 (DASS-21) (α = 0.74) [41]Child Physical, Mental and Social Health (Patient-Reported Outcomes Measurement Information System (PROMIS [42] and PROMIS Early Childhood [43]))Child Health-Related Quality of Life (Child Health Utility Instrument: CHU-9D) [44]

### Data collection plan retention

Participants are contacted twice, via a text message one week after the 3 month follow up is due and a telephone call 2 weeks later if the survey remains uncompleted. Participants choosing to withdraw from the study can do so without any repercussion and data will be destroyed. Participants identified retrospectively as meeting the exclusion criteria will be excluded from the study and additional participants will be recruited to fulfil the sample size (Table 1).

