### Eligibility criteria

Eligible participants are patients aged between 3 and 10 (inclusive) years old undergoing elective day-case procedures at a quaternary paediatric facility who do not meet the following exclusion criteria. Exclusion criteria consist of children (1) with a diagnosed pervasive developmental disorder or global developmental delay documented in their medical records, (2) requiring emergency surgery, (3) under the care of the Department of Child Safety, (4) who have a parent with insufficient English to provide consent without the aid of a translator, (5) deemed by anaesthetist as requiring pre-medication (i.e. midazolam) prior to a general anaesthetic, and (6) deemed highly anxious by the anaesthetist who will not benefit from additional personnel.

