### Statistical methods

#### Statistical methods for primary and secondary outcomes

Interrater reliability will be conducted by having two researchers independently scoring every anaesthetic induction for observational measures including mYPAS-SF, PACBIS and ICC. Following training in the measures, reliability will be attained by the researchers independently scoring sets of five videos, and statistically comparing results using intra-class correlations, as recommended for ordinal data [46]. The researchers will discuss any discrepancies in scoring, before independently scoring another set of five videos, until reliability is achieved. To test for inter-rater drift, reliability was assessed at 20% intervals throughout data collection.

Between group comparisons of primary and secondary outcomes will be compared using general linear modelling, to account for relevant control variables. Secondary outcomes that are non-continuous will be analysed using Pearson’s chi-squared analysis. The primary analysis will be ‘intention-to-treat’. A within-trial cost-effectiveness analysis will be conducted. Resource consumptions (and cost) will be collected for both arms (standard and interventions). Primary outcomes of behaviour and anxiety, and the secondary outcome (quality of life) will be used. Incremental cost and effectiveness (outcomes) will be calculated, and the incremental cost per effectiveness ratio (ICER) will be the primary result. Data will be reported in accordance with the Consolidated Standards of Reporting Trials (CONSORT) 2010 statement [47].

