## Data Availability

Participants or the research team may request to access data pertaining to the project. Protocol amendments Protocol amendments are submitted to the Human Research Ethics Committee of our institution. Consent or assent The research assistant will seek prospective written and informed consent from the patient’s parent or guardian prior to enrolment in the study, with consent able to be withdrawn. All withdrawal data will be collected and included in the CONSORT diagram [47]. Participant data will not be identified by name. Confidentiality De-identified raw data will be stored within a data repository and made available to other researchers upon reasonable request and following review of such a request by the original ethics committees. Ancillary and post-trial care If participants experience persistent distress after the completion of surgery and discharge from the hospital, a member of the research team (Psychologist) will follow up with any parents/guardians to ensure access to necessary support if required.

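### Removing and replacing randomised participants found ineligible later, and destroying withdrawals' data, conflicts with the stated intention-to-treat analysis and can bias it if removals differ by arm

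*Protocol article*

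**What the plan says.** In the protocol article, the section Data collection plan retention fixes two rules. On eligibility: "Participants identified retrospectively as meeting the exclusion criteria will be excluded from the study and additional participants will be recruited". On withdrawal: "Participants choosing to withdraw from the study can do so without any repercussion and data will be destroyed".

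The statistical methods section says "The primary analysis will be ‘intention-to-treat" and adds no modification or exception.

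Under Implementation, "After consent is obtained, the research assistant will open a sealed envelope". Under Concealment mechanism, "masking the research assistant, patient and their parent to the treatment allocation will not be possible".

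Two of the six exclusion criteria are the anaesthetist's judgements about the child's state: that pre-medication is needed, and that the child is "deemed highly anxious by the anaesthetist who will not benefit from additional personnel". The primary outcome, as the sample size section defines it, is the child's anxiety at induction on the mYPAS-SF.

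The consent text under Data Availability says "All withdrawal data will be collected and included in the CONSORT diagram".

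**The concern.** An intention-to-treat analysis keeps every randomised participant in the arm allocated. A rule that takes randomised participants out and recruits others in their place does not do this. Replacement restores the headcount but not the comparability that randomisation gave.

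Such removals can be harmless when ineligibility rests on facts fixed before allocation and is judged by someone who knows neither arm nor outcome. The rule as written has neither limit. Two of the criteria it can invoke sit close to the primary outcome, so removals that differ by arm would shift the primary comparison itself.

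The withdrawal rule adds a second loss. A parent who withdraws during the 3-month follow-up would take with them an induction score that had already been recorded.

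**Working it through.** **Whom the rule reaches.** Participant timeline, Recruitment and Table 1 place screening and consent before allocation, and the envelope is opened once consent is given. Someone already in the study and later found ineligible will therefore normally have been randomised. The only exception is the short interval between consent and opening the envelope.

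**Which safeguards are stated.** The rule does not restrict itself to pre-allocation facts and names no blinded assessor. The research assistant, who is not masked, collects outcome data (Data collection and methods) and carries out quality checks on source data (Data management). That person is well placed to notice late ineligibility. Who applies the rule is not said.

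**What withdrawal deletes.** The mYPAS-SF is scored at induction (t2) and follow-up runs to about day 92 (t4). Withdrawal at any point between the two would, as written, erase a recorded primary outcome.

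**Size of a possible bias.** The sample size section gives means of 55 and 40, an effect size of 0.61 and 50 per group. The implied SD is 15 / 0.61 = 24.6. As a check on those inputs, the normal approximation gives power of 92.0% one-sided and 86.2% two-sided at 0.05. The stated power above 90% is therefore reproduced only one-sided. Sidedness is not stated; that is a separate matter and nothing below depends on it.

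The documents give no removal rate, so the fractions f = 2%, 5% and 10% are assumptions. Removal is taken to affect one arm only, and replacements are taken to be subject to the same rule.

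- Moderate case: removed children score g = 15 to 25 points above their arm mean (assumed). Shift = f × g / (1 − f). Example: 0.10 × 25 / 0.90 = 2.8.
- Extreme case: exactly the top fraction f of a normal distribution is removed. Shift = SD × φ(z) / (1 − f), with z the upper-f point. Example: 24.6 × 0.1755 / 0.90 = 4.8.
- Type I error in the extreme case: SE = 24.6 × √(2/50) = 4.92 and d = shift / SE. The two-sided rate is about Φ(d − 1.96) + Φ(−d − 1.96), ignoring the smaller variance after trimming.

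| Removed from one arm | Moderate shift (points) | Extreme shift (points) | Type I error, extreme case |
|---|---|---|---|
| 2% | 0.3–0.5 | 1.2 | 5.7% |
| 5% | 0.8–1.3 | 2.7 | 8.4% |
| 10% | 1.7–2.8 | 4.8 | 16.4% |

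Against the 15-point target, 2.8 points is 19% and 4.8 points is 32%. Removing high scorers from the control arm shrinks an apparent benefit; removing them from the Take5 arm enlarges it. If removal is equal in both arms and unrelated to allocation, the expected shift is zero.

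**The case against.** The strongest defence is that the rule concerns facts that were true at screening and came to light later, such as a documented developmental diagnosis or Child Safety care. Several sections fit that reading. The anaesthetist settles pre-medication before the family is approached (Participant timeline), and eligibility is confirmed with the consultant anaesthetist (Recruitment). The Harms section has distress in either arm treated under institutional guidelines and recorded as feasibility data, with no mention of exclusion. Anaesthetic doctors and nurses, whose judgement drives the two anxiety-related criteria, are blinded to allocation.

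This has force. A reader might infer that a child who becomes very anxious, or is given pre-medication, after the envelope is opened is dropped and replaced. No section says so, and those just cited point the other way. What stands is that the rule's wording does not exclude that use. Nor would blinding alone make it safe: if Take5 works, fewer Take5 children become highly anxious, so even a blinded judgement made after allocation would remove more controls.

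On withdrawals, a reader might suppose that they are mostly distress-related; the documents give no support for that. Few withdrawals before the primary outcome are likely, since the video is shown about 15 minutes before surgery. Destruction may also reflect consent terms that were not available for review. A reader might further see a flat contradiction between destroying withdrawal data and collecting them. The Data Availability sentence refers to the CONSORT diagram, however, and can be read as counts and reasons only. That calls for clarification and is not a proven conflict.

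Details of analysis populations are often left to a SAP. Here, though, the article itself states both the removal rule and the unmodified intention-to-treat analysis, so the conflict lies in what is written.

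**Conclusion.** The point holds as a conflict between two stated rules: randomised participants may be removed and replaced, and recorded data destroyed, while the primary analysis is declared intention-to-treat. That conclusion rests on the text alone.

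Whether bias follows, and in which direction, cannot be determined from the article. It depends on how many are removed, whether removal differs by arm, and how far the removed children's scores lie from their arm mean. On the assumptions shown, one-arm removal of 2–10% moves the difference by about 0.3–2.8 points. The 4.8-point figure is an extreme, requiring that exactly the most anxious 10% of one arm are removed, and should not be read as an expected bias. The SD of 24.6 is implied by the plan; the removal rates and score gaps are not in it.

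**What to change.** Replace the retention rules with wording to this effect:

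- All randomised participants are analysed in the arm allocated.
- A participant may be removed only for an exclusion criterion already met before allocation. The judgement is made by someone blind to arm and outcome, and removals are reported by arm.
- Randomised participants are not replaced.
- On withdrawal, further collection stops. Data already collected are kept unless the parent asks for deletion, as consent allows.
- The Data Availability sentence means counts and reasons for withdrawal, so that it agrees with the retention section.

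The cost is mainly wording. A line of the consent form may need changing, and a few ineligible children may remain in the analysis. Giving up replacement costs little power. If 5% of 50 per arm lacked the primary outcome (an assumed rate), power would go from 92.0% to 90.8% one-sided, or from 86.2% to 84.4% two-sided.
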